### Statistical analysis

Changes in all cardiac metrics between arms will be compared using *t* tests for independent samples. An intention-to-treat analysis will be performed for the primary and secondary endpoints. Subgroup analyses will be performed for important covariates, including heart failure etiology, sex, age, paroxysmal vs persistent AF, and duration of AF. Subsequently, prediction of outcomes will be performed using regression analyses, considering potential confounders and/or mediators. This procedure will have 2 steps. First, we will conduct exploratory analyses through the use of univariate models and graphical checks of pattern between each candidate predictor and outcome variable. On the basis of these results, and after checking that linearity assumptions are correct, we will examine multivariable associations, taking account of potential confounding factors. Predictors in univariate analysis with *P* < .10 will be further tested in a prespecified multivariable regression model. Predictors will be entered into the model in groups determined by time ordering and/or their clinical relevancy. *P* < .05 will be considered statistically significant.

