**Results:**

Patients will undergo baseline assessment including transthoracic echocardiography (TTE), device check, blood tests, electrocardiogram (ECG), 6-minute walk test, and symptom questionnaire. They will then undergo either AV node ablation or AF ablation according to their allocated group. Follow-up will occur at 1 week (TTE and ECG) and at 6 months (repeat of baseline investigations). The primary endpoint will be change in left ventricular ejection fraction on TTE.

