### Trial design

Seventy patients with existing CRT devices (implanted for dyssynchronous heart failure) and suboptimal (<95%) biventricular pacing due to AF will be included in the study. Patients will be randomized to either AV node ablation or AF ablation in a 1:1 ratio and will be followed up at 6 months.

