### Eligibility

Inclusion and exclusion criteria are shown in Table 1. Eligible patients identified via cardiology outpatient clinics, pacing clinics, or inpatient wards will be informed about the study and provided with a patient information sheet. After reading the information sheet and after questions have been addressed, eligible patients will provide written informed consent for participation in the study. The protocol and data collection are summarized in Figure 1. Both conventional CRT “responders” and “nonresponders” will be included, as patients may experience a deterioration in biventricular pacing owing to new-onset or worsening AF after the initial assessment of response.

**Table 1 tbl1:** Patient eligibility

Inclusion criteria	Exclusion criteria
Age 18–85 years	Life expectancy <1 year
Ability to provide informed consent to participate and willing to comply with the clinical investigation plan and follow-up schedule	Permanent atrial fibrillation
QRS duration >120 ms on surface ECG, severe left ventricular systolic impairment (EF ≤35%), and clinical symptoms of heart failure despite optimum medical therapy (NYHA class II–IV) at time of CRT implant or upgrade	Presence of atrial or ventricular thrombus
Successful CRT implant or upgrade including atrial lead	Mechanical aortic valve replacement
Biventricular pacing percentage <95% secondary to atrial fibrillation at least 3 months post implant or upgrade, despite optimal pharmacological rate control	Severe peripheral vascular disease
Clinically indicated for AV node ablation	Female participants who are pregnant, lactating, or planning pregnancy during the course of the study
	LA diameter >6 cm
	Persistent AF duration >3 years
	Participation in other studies with active treatment / investigational arm

AF = atrial fibrillation; AV atrioventricular; CRT = cardiac resynchronization therapy; ECG = electrocardiogram; EF = ejection fraction; LA = left atrial; NYHA = New York Heart Association.

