### Baseline data collection

At baseline visit the patients will undergo clinical assessment, medication history, electrocardiogram (ECG), 6-minute walk test, Minnesota Living with Heart Failure Questionnaire, blood tests (including serum NT-proBNP), device check, and transthoracic echocardiogram. Cardiac device metrics collected will include AF burden, AF duration, biventricular pacing percentage, and previous ICD therapies. Echocardiographic metrics will include 2-dimensional LV end-diastolic volume, LV end-systolic volume, LV ejection fraction, and left atrial size. After the baseline visit, patients will be randomized 1:1 using dedicated software to either AV node ablation or AF ablation. Randomization will be stratified using the minimization method by heart failure etiology (ischemic or nonischemic) and by AF type (paroxysmal or persistent).

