### Sample size justification

Previous comparisons between AV node ablation and AF ablation in patients with AF and heart failure (not indicated for CRT) found a -1% change in LV ejection fraction with AV node ablation compared to 8% with AF ablation.^26^ Measurements of changes in ejection fraction in CRT patients receiving AV node ablation or AF ablation have a variability of 7.1%–10.7%,^25^^,^^28^ giving a maximum variability of 11%. Assuming a normal distribution, a group size of 32 for each arm would achieve 90% power to reject the null hypothesis of equal means, with an alpha value of 0.05 to detect the 9% difference in change in LV ejection fraction using a 2-sided independent *t* test. This sample size will also ensure satisfactory 80% statistical power for detection of 7.5% difference in change in LV ejection fraction. To allow for an approximately 10% drop-out rate we will recruit a total of 70 patients.

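### The primary comparison is an unadjusted t test on change in LVEF; it is valid, but adjusting for baseline LVEF and the two minimization factors would gain precision at no cost

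*Protocol article*

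**What the plan says.** The abstract defines the endpoint: "The primary endpoint will be change in left ventricular ejection fraction on TTE". Under Statistical analysis, the between-arm method is fixed: "Changes in all cardiac metrics between arms will be compared using" t tests for independent samples. The Sample size justification uses the same two-sided test.

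Under Baseline data collection, LVEF is measured in every patient before randomization: "Echocardiographic metrics will include 2-dimensional LV end-diastolic volume, LV end-systolic volume, LV ejection fraction, and left atrial size". The same section describes the allocation: "Randomization will be stratified using the minimization method by heart failure etiology (ischemic or nonischemic) and by AF type (paroxysmal or persistent").

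No section puts baseline LVEF or either minimization factor into the primary comparison. Etiology and AF type return only as subgroup variables. Regression with covariates is described only for the later prediction of outcomes.

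**The concern.** Two pieces of information that the trial already collects are not used where they would help most.

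- **Baseline LVEF.** A change score subtracts baseline with a slope fixed at 1. If the true slope of 6-month LVEF on baseline is lower, the change score over-corrects. The error variance is then larger than it need be, and a chance difference in baseline LVEF between the arms carries into the estimate. Baseline LVEF is not a minimization factor, so with about 32 patients per arm such a difference can easily arise.
- **Minimization factors.** Minimization makes the arms more alike on etiology and AF type than unrestricted allocation would. The t test does not know this. If the factors predict change in LVEF, its standard error still contains variance that the design has balanced out.

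What is at stake is precision on the primary endpoint of a 70-patient trial whose authors already plan how to interpret a null result.

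**Working it through.** **Inputs from the protocol article (Sample size justification, Trial design).** The target difference is 9 points, from a study that "found a -1% change in LV ejection fraction with AV node ablation compared to 8% with AF ablation". The SD of change is 11 ("giving a maximum variability of 11"%). There are 32 patients per arm, allocation is 1:1 and alpha is 0.05 two-sided. The article also states 80% power for 7.5 points.

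**Assumptions, because the document gives no figure.** The correlation r between baseline and 6-month LVEF is taken as 0.3 to 0.8, with 0.9 as a further case. The SDs at the two times are equal. The share of the variance of change explained by the two minimization factors is 5%, 10% or 20%.

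**Step 1: the plan's own figure.** By the normal approximation, n per arm = 2 × 11² × (1.960 + 1.282)² / 9² = 31.4, rounded up to 32. The exact t solution is 32.4. Exact power at 32 per arm is 89.6% for 9 points, so the stated size reproduces for an unadjusted test with the full SD of 11. For 7.5 points, exact power is 76.6% (77.9% by the normal approximation), against the stated 80%.

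**Step 2: adjusting for baseline LVEF.** With common SD s, Var(change) = 2s²(1 − r), and the ANCOVA residual variance is s²(1 − r²). The ratio is (1 + r)/2, so the effective SD is 11 × √((1 + r)/2). Holding the SD of change at 11 implies s = 11/√(2(1 − r)).

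| r | Variance ratio | Effective SD | Power, 9 points | Power, 7.5 points | Implied baseline SD |
|---|---|---|---|---|---|
| t test | 1 | 11 | 89.6% | 76.6% | – |
| 0.3 | 0.65 | 8.87 | 97.9% | 91.5% | 9.3 |
| 0.5 | 0.75 | 9.53 | 96.1% | 87.3% | 11.0 |
| 0.7 | 0.85 | 10.14 | 93.8% | 82.9% | 14.2 |
| 0.8 | 0.90 | 10.44 | 92.4% | 80.8% | 17.4 |
| 0.9 | 0.95 | 10.72 | 91.1% | 78.7% | 24.6 |

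**Step 3: chance baseline imbalance.** A baseline difference D between the arms shifts the expected change-score difference by (1 − r) × D, in the opposite direction. One standard error of D is s × √(2/32).

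- r = 0.3: 9.3 × 0.25 = 2.32, so the shift is 0.7 × 2.32 = 1.6 points.
- r = 0.8: 17.4 × 0.25 = 4.35, so the shift is 0.2 × 4.35 = 0.9 points.

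**Step 4: the minimization factors.** Simulation used 64 patients, two binary factors split 50:50, a biased coin of 0.8 and no treatment effect. In one set of 6,000 runs per setting with r = 0.6:

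| Variance explained | t test: mean model SE | t test: actual SE | Ratio | t test: type I error | ANCOVA: type I error |
|---|---|---|---|---|---|
| 0% | 2.74 | 2.78 | 0.99 | 5.2% | 5.6% |
| 5% | 2.74 | 2.68 | 1.02 | 4.4% | 4.9% |
| 10% | 2.74 | 2.63 | 1.04 | 4.2% | 4.5% |
| 20% | 2.74 | 2.51 | 1.09 | 3.5% | 5.1% |

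Monte Carlo error at a 4% rate is √(0.04 × 0.96/6000), about 0.25 percentage points. Across repeated simulations of the same setting, the t test's type I error was 4.4-4.6% at 5% explained, 3.8-4.4% at 10% and 3.1-3.5% at 20%. At 0% the t test's error is nominal within simulation error.

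The same simulation supports Step 2. With r = 0.6 and factors that explain nothing, ANCOVA had power of 95.0% at 9 points and 84.8% at 7.5. The formula gives 95.0% and 85.1%.

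**The case against.** The strongest reply is that nothing here is an error. The article sizes the trial on a t test and analyses it with the same test, and the stated 32 per arm reproduces. The SD was rounded up from 10.7 to 11. Averaged over randomizations, the change-score comparison is unbiased. All of this stands, and it makes the point one of efficiency.

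Four stronger readings are tempting, and the document does not support them.

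- **That the standard error is wrong in a way that threatens validity.** The mismatch goes one way only: the standard error is too large and the test conservative. It vanishes if etiology and AF type do not predict change in LVEF, and the document gives no figure for how well they do.
- **That the plan ignores baseline LVEF, or that its estimator is biased.** A change score uses baseline with a fixed slope. The shift in Step 3 is conditional on the imbalance that happens to occur and averages to zero.
- **That the trial is underpowered for its 9-point target.** On its own inputs it is not.
- **That the mixed population makes the gain large.** Responders and nonresponders both enter because "patients may experience a deterioration in biventricular pacing owing to new-onset or worsening AF after the initial assessment of response", so baseline LVEF may well vary widely. With the SD of change held at 11, however, a wider baseline spread implies a higher r and a smaller gain, as the last column in Step 2 shows.

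It can also be said that covariate lists belong in an analysis plan not shown here. That would answer a silence, but the article names the test. The planned subgroup analyses and later prediction regressions are not an adjusted primary comparison.

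**Conclusion.** The point holds as a free improvement. The planned test is valid on average and does not raise the false-positive rate, but it is less precise than the collected data allow.

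With r assumed at 0.3-0.8, baseline adjustment cuts the variance by 10-35%. Power rises from 89.6% to about 92-98% at 9 points and from 76.6% to about 81-91% at 7.5 points. At r = 0.9 it reaches only about 91% and 79%. These figures also rest on equal SDs, an SD of change of 11 and 32 evaluable patients per arm.

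Leaving out the minimization factors makes the t test's standard error about 2-9% too large if they explain 5-20% of the variance. The direction of both effects is secure, but their size is not, because neither r nor the explained share is documented. The 80% power that the article states for 7.5 points is not reached by the planned test at 32 per arm, and baseline adjustment would reach it throughout r = 0.3-0.8.

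**What to change.** Make the primary analysis an ANCOVA of LVEF at the 6-month visit on arm, baseline LVEF, etiology (ischemic or nonischemic) and AF type (paroxysmal or persistent). Report the adjusted difference with its 95% confidence interval. Using change as the response in this model gives the same treatment estimate, so the endpoint definition need not alter. Apply the same model to the other continuous endpoints, each with its own baseline value, and keep the independent t test as a sensitivity analysis.

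This takes a sentence or two in the Statistical analysis section or the analysis plan, settled before outcome data are examined by arm. It costs three degrees of freedom and needs no new data and no more patients.

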## Objectives

The primary research objective is to compare the effects of AV node ablation and AF ablation on echocardiographic and symptomatic outcomes in patients with CRT and suboptimal (<95%) biventricular pacing. The principal hypothesis tested will be that AF ablation is superior to AV node ablation in improving LV ejection fraction (primary endpoint). Secondary endpoints will include changes in LV ejection fraction and LV end-systolic volume at 1 week; and changes in LV end-systolic volume, Minnesota Living with Heart Failure Questionnaire Score, NYHA class, 6-minute walk test, NT-proBNP, AF burden, biventricular pacing percentage, ventricular arrhythmias, and inappropriate ICD shocks at 6 months. Procedural complications will be recorded, and exploratory safety outcome differences will be analyzed.

If there is no overall benefit for AF ablation on intention-to-treat analysis, it is important to determine if this is because restoring sinus rhythm has no benefit over rate control, or if the benefits of AF ablation are diluted by a high rate of recurrence. We will therefore perform a subanalysis comparing the clinical endpoints between patients who underwent AF ablation and are in sinus rhythm at 6 months, vs those who underwent AF ablation and are in AF at 6 months, vs those who underwent AV node ablation. If significant benefits are observed for patients who maintain sinus rhythm after AF ablation, the next research objective will be to determine which baseline factors are most useful to predict the chance of success after AF ablation in this patient cohort. Baseline factors tested will include clinical factors (eg, duration of AF, paroxysmal vs persistent AF, age, comorbidities) and imaging characteristics on echocardiography (eg, LV size, LV function, left atrial size). We will also assess if improvement in LV ejection fraction correlates with a reduction in AF burden.

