The definition of “success” for AF ablation varies between studies and is often related to recurrence of a >30-second episode of atrial arrhythmia during the follow-up period.^32^ Given that all enrolled patients have CRT devices in situ, the RHYTHMIC study has the advantage of allowing continuous rhythm monitoring after ablation, and therefore the effect of ablation on AF burden can be determined. In a recent study of 207 patients with AF and existing pacemakers, ICDs, or implantable loop recorders, AF ablation significantly reduced the burden of AF in patients with both paroxysmal and persistent AF at 1-year follow-up (median AF burden 1.05% vs 0.10% and 99.9% vs 0.30%, respectively).^33^ Significant reductions compared to pre ablation were also found at 4-year follow-up (0.10% and 87.3%, respectively). In the context of patients with heart failure, persistent AF, and CRT, although long-term sinus rhythm maintenance may be difficult to achieve, a reduction in AF burden may be sufficient to achieve a benefit owing to improved biventricular pacing and atrioventricular synchrony. To this end, we will examine if changes in AF burden correlate with improvements in LV ejection fraction.

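### The only between-arm test named, an unadjusted t test on change, ignores baseline values already collected and suits raw NT-proBNP, AF burden and event counts poorly

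*Protocol article*

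**What the plan says.** The Statistical analysis section fixes the comparison in one sentence: "Changes in all cardiac metrics between arms will be compared using" independent-samples t tests. It names no baseline adjustment, transformation, ordinal method or count method for comparing arms. Linearity is to be checked only in the later prediction models.

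The Objectives list two secondary endpoints at 1 week ("Secondary endpoints will include changes in LV ejection fraction and LV end-systolic volume at 1 week"). At 6 months they list LV end-systolic volume (LVESV), the Minnesota score, and "NYHA class, 6-minute walk test, NT-proBNP, AF burden, biventricular pacing percentage, ventricular arrhythmias, and inappropriate ICD shocks at 6 months". That makes 2 + 9 = 11 secondary endpoints.

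The phrase cardiac metrics is not defined. The nearest usage is in Baseline data collection: "Cardiac device metrics collected will include AF burden, AF duration, biventricular pacing percentage, and previous ICD therapies", and "Echocardiographic metrics will include 2-dimensional LV end-diastolic volume, LV end-systolic volume, LV ejection fraction, and left atrial size". By that usage AF burden, biventricular pacing and ICD therapies fall under the t test. NT-proBNP and NYHA class are covered only by inference, but no other test is offered for them.

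**The concern.** Baseline LVEF, volumes, NT-proBNP, Minnesota score and walk distance are all measured before randomisation. A t test on change subtracts the baseline with a fixed coefficient of 1, which is less efficient than estimating that coefficient.

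Three further features make a mean of raw changes a poor summary for some endpoints:

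- **NT-proBNP.** If, as assumed here, it is right-skewed and treatment acts as a ratio, the patients with the largest values dominate the mean raw change.
- **AF burden.** The Discussion cites a device-based study in which burden before and after ablation, for paroxysmal and persistent AF in turn, was "median AF burden 1.05% vs 0.10% and 99.9% vs 0.30%, respectively". This trial enrols both types.
- **Arrhythmia and shock counts.** Eligibility requires a CRT device with an atrial lead, not a defibrillator, so some patients may be unable to have a shock. The Follow-up section moves the final visit to 6 months after a re-do ablation, which only the AF ablation arm can have.

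The article intends to use rhythm and AF burden to explain the LVEF result and to inform larger trials, so these endpoints need to be readable.

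**Working it through.** **1. The plan's own figure.** The Sample size justification says "a group size of 32 for each arm would achieve 90% power to reject the null hypothesis of equal means", for a 9-point difference, SD 11 and two-sided alpha 0.05.

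- n = 2(1.960 + 1.282)² × 11² / 9² = 31.4, so 32 per arm.
- Power at 32 = Φ(9 / (11 × √(2/32)) − 1.96) = Φ(3.27 − 1.96) = 90.5%. The noncentral t gives 89.6%.

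The figure reproduces, and a t test is valid for this endpoint.

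**2. What baseline adjustment adds.** Take equal SD σ at both visits and correlation r (not given in the article).

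- Variance of change = 2σ²(1 − r).
- ANCOVA residual variance = σ²(1 − r²).
- Ratio = (1 + r)/2, which is 0.75, 0.85 and 0.95 for r = 0.5, 0.7 and 0.9.

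For LVEF at r = 0.7 the effective SD falls from 11 to 11 × √0.85 = 10.1, and normal-approximation power rises from 90.5% to Φ(9 / (10.14 × 0.25) − 1.96) = 94.4%. This gain is modest.

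**3. NT-proBNP.** Assumptions: log-normal values, r = 0.7, true ratio 0.6 (log 0.6 = −0.511), 32 per arm, log-SD s.

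- SD of log change = s√(2 × 0.3) = 0.775s.
- Log-scale ANCOVA residual SD = s√(1 − 0.49) = 0.714s.
- At s = 1.0, normal-approximation power is Φ(0.511 / (0.775 × 0.25) − 1.96) = 75% for log change and Φ(0.511 / (0.714 × 0.25) − 1.96) = 82% for ANCOVA.

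The raw-change t test has no simple formula and was simulated together with the other two. Separate runs agreed within about 1 point:

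| log-SD | t test, raw change | t test, log change | ANCOVA, log scale |
|---|---|---|---|
| 0.8 | 59% | 90% | 94% |
| 1.0 | 36% | 74–75% | 80% |
| 1.2 | 21–22% | 58–59% | 64–65% |

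Most of the gain comes from the log scale (31 to about 39 points), and about 4 to 6 points from the adjustment. With no true effect, the raw-change t test rejected in 3.5–4.9% of simulated trials. At a milder log-SD of 0.6 the contrast shrinks to 87% against 99.6%.

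**4. AF burden.** As an illustration only, treat the cited medians as each type's values. The change is 0.10 − 1.05 = −0.95 points in paroxysmal and 0.30 − 99.9 = −99.6 points in persistent AF. With 30%, 50% or 70% persistent patients, the mean change after AF ablation is:

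- 0.7 × (−0.95) + 0.3 × (−99.6) = −30.5
- 0.5 × (−0.95) + 0.5 × (−99.6) = −50.3
- 0.3 × (−0.95) + 0.7 × (−99.6) = −70.0

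The effect within each type is the same, yet the headline number more than doubles with the enrolment mix. Entry requires pacing below 95% because of AF, so paroxysmal patients here probably have more burden than the cited 1%. The contrast between types would then be smaller, but of the same kind.

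**5. Counting time.** The article does not say when event counting starts. Suppose it runs from the first ablation to the final visit. Take 24.5% of the AF ablation arm having a re-do (the repeat rate quoted in the Discussion from another heart failure trial) and assume it occurs at 3 months. Mean counting time in that arm is then 6 + 0.245 × 3 = 6.7 months against 6.0, or 12% longer. With the re-do at 1 or 5 months it is 4% or 20% longer. A mean change in counts ignores this; a rate does not.

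**The case against.** The article condenses a fuller protocol, and an analysis plan may set methods by endpoint. The text says cardiac metrics, and the baseline section uses metrics for device and echocardiographic data only. On that narrow reading no test is named for NT-proBNP, and silence in an article is no defect. This stands to the extent that NT-proBNP coverage is an inference. What remains is that the one method stated is unadjusted and its scope is undefined.

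A reader might infer more: that the t test loses power on about half of the secondary endpoints. Five or six of the 11 are awkward variable types, but a loss is shown only for NT-proBNP, under assumed inputs.

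- **NYHA class.** Under an assumed four-category change distribution, the t test and Mann-Whitney had 57.2% and 57.3% power.
- **AF burden.** Under assumed bimodal distributions the t test did better: 47–67% against 28–34% for Mann-Whitney at 30% ablation success. In a separate check it had 32–63% against 25–32% for a van Elteren test stratified by AF type. So the documents do not support a claim that the t test would miss effects on burden, or that a stratified rank test would gain power.
- **Shocks.** At assumed incidences of 3%, 6% and 10% the t test is conservative (size 0.1%, 1.3%, 2.9%), but Fisher's exact test is more so (0.03%, 0.3%, 1.1%). With 64 × 0.03 = 1.9 to 64 × 0.10 = 6.4 patients affected, the limit is the number of events.

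Allocation is minimised on AF type, and subgroup analyses by AF type are planned, so the mix should not bias the comparison and part of the by-type reporting is already foreseen. That also stands.

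**Conclusion.** The point holds as one of efficiency and interpretability, mainly on secondary endpoints. The primary LVEF comparison is valid, its sample size reproduces, and false-positive error is not inflated.

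The largest effect is on NT-proBNP. If raw change is t-tested, about 35 to 44 points of power are lost against log-scale ANCOVA, given log-SD 0.8–1.2, correlation 0.7 and a true ratio of 0.6. The loss is smaller with less skew, at about 12 points for log-SD 0.6. For the other continuous endpoints adjustment removes roughly 5–25% of the variance for correlations of 0.9 down to 0.5, assuming equal SDs at both visits. For AF burden and event counts no power claim is made; there a mean change is hard to read.

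**What to change.** Define which endpoints the stated comparison covers, and replace the single sentence with a short table fixed before outcome data are seen by arm:

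- **LVEF, LVESV, Minnesota score, 6-minute walk:** ANCOVA on the follow-up value, adjusted for baseline.
- **NT-proBNP:** ANCOVA on the log scale, adjusted for log baseline, reported as a ratio of geometric means.
- **AF burden and biventricular pacing:** keep the overall comparison and also summarise by AF type.
- **Ventricular arrhythmias and inappropriate shocks:** patients with at least one event, and rates per patient-time with the counting window stated. Restrict shocks to patients with a CRT-defibrillator.

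The baseline measurements are already planned; only device type and counting dates need to be on record. The cost is a page of text and several effect measures instead of one. The event summaries will still have little power and should be presented as descriptive.

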### Follow-up

Patients will undergo transthoracic echocardiogram and ECG 1 week post ablation, to assess acute response. They will then be seen at the 6-month visit, where they will undergo repeat clinical assessment, ECG, 6-minute walk test, blood tests (including serum NT-proBNP), device check, and transthoracic echocardiogram. Patients in the AF ablation arm who have a recurrence of AF during the follow-up period will be permitted 1 re-do ablation, and their follow-up visit will occur 6 months after the second procedure.

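### As stated, the intention-to-treat t test on change is a completer comparison by assigned arm; for LVEF and LVESV, an adjusted repeated-measures model would use the 1-week echo already collected

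*Protocol article*

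**What the plan says.** All references are to the protocol article.

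- **Statistical analysis.** "Changes in all cardiac metrics between arms will be compared using" independent-samples t tests, and the next sentence adds: "An intention-to-treat analysis will be performed for the primary and secondary endpoints". The regression models later in that section are for predicting outcomes, not for comparing the arms.
- **Abstract.** "The primary endpoint will be change in left ventricular ejection fraction on TTE".
- **Sample size justification.** "Assuming a normal distribution, a group size of 32 for each arm would achieve 90% power", "with an alpha value of 0.05 to detect the 9% difference in change in LV ejection fraction", "using a 2-sided independent" t test. Then: "To allow for an approximately 10% drop-out rate we will recruit a total of 70 patients".
- **Follow-up.** "Patients will undergo transthoracic echocardiogram and ECG 1 week post ablation". The main follow-up visit is at 6 months. Only AF-ablation patients may have a re-do, and their final visit is then counted from the second procedure.
- **Objectives.** LVEF and LVESV at 1 week are separate secondary endpoints. No other secondary endpoint is listed at 1 week.
- **Baseline data collection.** Allocation is minimized on heart failure etiology and AF type.

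**The concern.** A t test on change needs a baseline and a follow-up value for each patient. The trial is sized on that same test with 64 patients and recruits 70, so the plan expects about 6 randomized patients to have no primary endpoint value. The article does not say how such patients enter an analysis that it calls intention-to-treat.

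The matter is more than a label if loss is related to outcome. Patients who die or become too ill to attend plausibly have a poorer LVEF course. Loss could also differ between arms. A re-do lengthens follow-up in the AF-ablation arm only, and the Discussion describes AF ablation as the procedure with the higher complication risk. If AF-ablation patients who respond poorly are the ones lost, the completer contrast moves towards the hypothesized result. The plan already collects an early LVEF that would inform on some of these patients, but it does not use it for the final contrast.

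**Working it through.** **Inputs from the article.** Target difference 9 points, SD of change 11, two-sided alpha 0.05, power 90%, 32 analysed per arm, 70 recruited 1:1 (35 per arm).

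**1. The plan's own figure.** n per arm = 2 × (1.960 + 1.282)² × 11² / 9² = 31.4, rounded up to 32. Power at 32 is 90.5% by the normal approximation and 89.6% by the exact t distribution. The figure reproduces.

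**2. Planned loss.** 70 − 64 = 6, and 6/70 = 8.6%, which fits the stated drop-out of about 10%.

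**3. Precision at stake.** The standard error of the contrast is 11 × √(2/32) = 2.75 points. If all 35 per arm had a final value, exact power would be 92.1% instead of 89.6%. That is an upper bound on the gain, because a 1-week value recovers only part of the missing information.

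**4. Simple bias arithmetic (assumed losses).** If k of 35 patients are lost and their unobserved changes are d points worse than those of the arm's completers, the completer mean is too high by k × d / 35.

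- Informative loss in one arm only: 3 × 5/35 = 0.43 to 4 × 10/35 = 1.14 points.
- Loss of 3 in each arm, equally unfavourable: net 0.
- Loss of 4 against 2, equally unfavourable: 2 × 5/35 = 0.29 to 2 × 10/35 = 0.57 points.

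**5. Simulation (assumed inputs).** 35 per arm, 3 lost per arm, SD 11 at both visits, correlation between 1-week and 6-month change of 0.3, 0.5 or 0.7, and 3,000 replicates. The model is a simplified likelihood estimator that uses the 1-week change, without further covariates.

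| Scenario | Corr. 0.3 | Corr. 0.5 | Corr. 0.7 |
|---|---|---|---|
| Random loss, true difference 9: t test mean (SE) | 8.99 (2.688) | 9.00 (2.764) | 9.01 (2.786) |
| Same: model mean (SE) | 9.00 (2.680) | 9.01 (2.731) | 9.00 (2.730) |
| 3 worst 1-week AF-ablation patients lost, true difference 9: t test | 9.52 | 9.84 | 10.39 |
| Same: model | 8.98 | 8.93 | 9.12 |
| Same loss, no true difference: t test | 0.62 | 0.93 | 1.27 |
| Same: model | 0.07 | 0.03 | 0.02 |
| Same: t test type I error | 5.4% | 6.4% | 8.1% |

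Under random loss the model lowers the SE by 0.3%, 1.2% and 2.0%. Monte Carlo error is about 2.7/√3000 = 0.05 on the means and √(0.05 × 0.95/3000) = 0.4 percentage points on the type I error, so 5.4% cannot be told apart from 5%. The t test minus the model at a true difference of 9 is 0.54, 0.91 and 1.27, close to the shifts seen with no true difference.

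**The case against.** The strongest reply is that this is a condensed article. It names a test and a principle, and it nowhere says that patients without a final echo are excluded. A t test can be run on imputed data, and inflating 64 to 70 is ordinary planning that does not define an analysis set. The Objectives use intention-to-treat mainly to contrast comparison by allocated arm with a subanalysis by rhythm at 6 months. All of this stands. A reader might infer that the article contradicts itself, or that it commits to dropping every patient without a 6-month value. It does not go that far, and silence on imputation is not an error.

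Three further inferences also fail:

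- *That the 1-week echo would keep most lost patients in.* The article does not say when drop-out occurs, and patients lost before that echo stay missing.
- *That it would help every endpoint.* Only LVEF and LVESV are listed at 1 week.
- *That a one-arm shift of 0.43 to 1.14 points is the bias in the treatment contrast.* It is so only if losses in the other arm are uninformative. With equally unfavourable losses in both arms, the net shift in step 4 is 0 to 0.57 points, at most about 0.2 standard errors.

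The evidence for uneven loss is also limited. The Discussion's 2%–3% serious complication risk is 0.7 to 1.05 of 35 patients, and not all of them would be lost. The simulated loss, exactly the three worst early responders in one arm, is extreme. It also suits the model, because loss there depends on an observed value.

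None of this defends the unadjusted t test as the better choice. It narrows the point to a stated method that can be improved with data already being collected.

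**Conclusion.** The point holds in a limited form. Followed as written, and unless imputation is specified elsewhere, the primary test compares completers by assigned arm. It uses baseline only by subtraction, and leaves out the 1-week LVEF and LVESV and both minimization factors.

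The case rests on possible bias and accurate description, not power. With loss unrelated to outcome there is no bias and almost no gain from the 1-week value. With loss that depends on early response and differs between arms, the plausible shift in the contrast is roughly 0 to 1.3 points, up to about 14% of the 9-point target (1.3/9) or about half a standard error (1.3/2.75). The upper end needs one-sided informative loss and a correlation of 0.7. The numbers lost per arm, the correlation and the loss pattern are all assumptions. The change is worth making because it costs little, not because the trial's result is shown to be at risk.

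**What to change.** - **LVEF and LVESV.** Replace the t test on change with a likelihood-based repeated-measures model on the 1-week and final-visit values. Include baseline as a covariate (or constrained equal between arms), arm by visit, heart failure etiology and AF type. The final-visit contrast for LVEF is primary. Treat the final visit as a nominal visit, because after a re-do it falls later and in one arm only. Patients with a 1-week echo but no final echo then contribute.
- **Endpoints without a 1-week value.** Where the outcome is continuous, use baseline-adjusted ANCOVA with the minimization factors. Describe the analysis as by assigned arm among patients with follow-up.
- **Sensitivity.** Add one analysis that gives deaths and losses for worsening an unfavourable value. The main model does not protect against loss that depends on unobserved outcomes.
- **Wording.** State how randomized patients without a final value are handled. If the t test is kept, call it a complete-case analysis by assigned arm.

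The cost is some wording and slightly more analysis, with no new visits or data. The drawback is reliance on a missing-at-random assumption, which the sensitivity analysis probes.
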